
## Methods and Analysis

### Participants and Study Design

This is a prospective cohort study made up of four groups with a specific diagnosis (stroke, spinal cord injury, knee OA, or lower limb amputation) and a group of healthy volunteers.

Patients admitted to the conventional rehabilitation program of the Instituto de Medicina Física e Reabilitação (IMREA) will be invited to participate in the study and included after signing the informed consent form previously approved by the Hospital das Clínicas da Faculdade de Medicina da Universidade de São Paulo Ethics Committee for Research Protocol Analysis CAAE: 86832518.7.0000.0068. For this study, 400 patients will be recruited, 100 patients with a stroke diagnosis, 100 with knee OA, 100 with spinal cord injury, and 100 amputee patients. The control group will be made up of 100 healthy subjects paired by sex and age.

Patients who agree to participate in the study will undergo a series of assessments at two time points: before and after the IMREA rehabilitation program. An individualized approach characterizes this program, considering the injury's etiology, the type of disabilities the patient has, general clinical conditions, likely prognosis, and the patient's socioeconomic factors. The control group will only perform neurophysiological (EEG, fNIRS, and TMS) and functional assessments once.

It is important to note that all patients involved in the research will receive the same type of treatment as patients who are not participating in the research.

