### Sample Size

The sample size of 100 patients for each type of injury was determined, given this is an observational study (prospective cohort) and, thus, the primary analysis being a linear regression. Therefore, 100 participants in each group will allow for the modeling of 10 covariates, which will yield an effect size of ~0.3, which we believe is enough, mainly due to the use of neurophysiological variables and our knowledge of previous studies. Our group recently performed two studies with multivariate analyses, one with 35 and another with 55 patients, to assess neurophysiological markers (EEG and TMS), which allowed us to identify the role of these markers in the rehabilitation of conditions such as stroke.

Thus, using a larger sample (100 subjects), compared with our previous studies, associated with a larger detailing of clinical and neurophysiological information, will aid in the better comprehension of cerebral plasticity. We also believe this sample size will yield similar results for patients with knee OA, spinal cord injury, and amputation. Furthermore, it will allow for the identification of transdiagnostic markers, not aiming to compare the different injury groups but to determine the neurophysiological alterations they have in common.

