### Statistical Analysis

For this analysis, we will use the multivariate regression model in which motor improvement will be the dependent variable and changes in inhibitory activity (resulting from neurophysiological assessments performed before and after treatment) will be the independent variables.

To control the impact of different conditions on the multivariate model, we will create a “dummy variable” for each disease etiology. Moreover, demographic characteristics (age, education, sex, and ethnicity) and clinically relevant characteristics (duration of illness, comorbidities, and the use of medications) will be tested, as well as specific aspects for each disease, such as the stroke side, the level of spinal cord injury, the degree of bone deformity of knee OA, and the level of lower limb amputation. The neurophysiological biomarkers described earlier will be tested in the same model.

Although this study's aim is not to test interventions but to identify changes in biomarkers related to functional improvement (regardless of the therapy performed), the different therapies performed by patients will be quantified, including information such as the number of sessions, frequency, duration, among others, which can be used in future analyses.

For secondary analyzes, functional improvement can be assessed by the several, general and specific, scales used depending on the evaluated disease. In this situation, we will use the calculation of the functional modification's effect size and not the absolute values of the scale for the analysis in the multivariate model.

Also, the motor function of the upper limb will only be assessed for patients with stroke and spinal cord injury, the main scale used being the Fugl–Meyer Assessment. In this case, an analysis similar to the one described earlier will be performed but only including these two populations.

Some of the scales, such as those for mood, pain, cognition, and sleep, will be used to characterize the sample, in addition to possibly being used to control confounders in the multivariate model. Besides, mood, pain, and cognitive disorder are commonly present in these populations, so we will perform an exploratory analysis using a similar statistic method but with scales related to these aspects as dependent variables.

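### The pooled model adjusts for etiology with dummy variables only, so it assumes one common marker slope and cannot show that a marker is transdiagnostic

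*Protocol article*

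**What the plan says.** The Sample Size section gives the purpose of studying four conditions together: "it will allow for the identification of transdiagnostic markers, not aiming to compare the different injury groups", the target being what the groups share. The Abstract calls these markers transdiagnostic, and the Introduction speaks of a relation that does not depend on etiology.

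The Statistical Analysis section describes one regression in which "motor improvement will be the dependent variable and changes in inhibitory activity" are the explanatory variables. On the four conditions it says "To control the impact of different conditions on the multivariate model, we will create a" dummy variable for each etiology. Demographic and clinical covariates, and some disease-specific ones, are to be tested, and the markers go into the same model. For this main model the article states no marker-by-etiology term, no slope per condition and no rule for deciding that a relation is shared. The only analysis restricted to particular conditions on clinical grounds is the upper-limb one, in stroke and spinal cord injury.

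Recruitment is equal: "400 patients will be recruited, 100 patients with a stroke diagnosis, 100 with knee OA, 100 with spinal cord injury", plus 100 amputees. On size, the article says "100 participants in each group will allow for the modeling of 10 covariates, which will yield an effect size of ~0.3".

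**The concern.** Whether a marker-improvement relation is shared by four conditions is a question about four slopes. A model with etiology dummies has four intercepts and one slope. Its marker coefficient is a weighted average of the four condition-specific slopes, with roughly equal weights when the groups are equal in size and marker variance. A significant average says that the mean slope differs from zero. It does not say that each slope does, or even that all four have the same sign.

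Heterogeneity is plausible here by design. The Introduction says the conditions were chosen because the lesion lies at different levels of the nervous system, and the Discussion names variability of clinical phenotype as a limitation and answers it with covariate adjustment, which leaves the common slope in place. At stake is the study's headline conclusion: a marker that works in half the sample, or reverses in one disease, could be reported as independent of etiology.

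**Working it through.** **Inputs.** Four conditions of 100, N = 400 (Participants and Study Design). Effect size about 0.3 and 10 covariates (Sample Size). Significance level and power are not stated; two-sided 0.05 is assumed. Further assumptions: equal marker variance across conditions, marker and outcome standardised within condition, covariates independent of the marker, no dropout (the article gives no rate).

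**1. The plan's own figure.** The metric behind 0.3 is not stated, so it cannot be strictly reproduced. Read as a partial correlation for one coefficient among 10 predictors, n = 100: f² = 0.09/0.91 = 0.099, noncentrality = 100 × 0.099 = 9.9 on 1 and 89 df, power 87.5%. The detectable partial r is 0.27 at 80% power and 0.31 at 90%. So 0.3 is a plausible per-condition slope and is used below.

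**2. Pooled slope.** With equal groups the common-slope estimate has mean b̄ = (b₁+b₂+b₃+b₄)/4 and standard error of about 1/√400 = 0.05. Power ≈ Φ(b̄/0.05 − 1.96).

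- (0.3, 0.3, 0, 0): b̄ = 0.15; Φ(3.0 − 1.96) = Φ(1.04) = 85%
- (0.3, 0.3, 0.3, −0.3): b̄ = 0.15; again 85%
- (0.3, 0, 0, 0): b̄ = 0.075; Φ(1.5 − 1.96) = Φ(−0.46) = 32%
- (0.5, 0, 0, 0): b̄ = 0.125; Φ(2.5 − 1.96) = Φ(0.54) = 71%

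**3. Heterogeneity test.** For the 3-df marker-by-etiology F test the noncentrality is about 100 × Σ(bᵢ − b̄)², taking residual variance near 1.

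- 0.3 in one condition, or in three: 100 × 0.0675 = 6.75, power about 57%
- 0.3 in two: 100 × 0.09 = 9.0, power about 71%
- (0.3, 0.3, 0.3, −0.3): 100 × 0.27 = 27, power above 99%

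**4. Simulation** (thousands of runs per scenario, etiology intercepts, two-sided 0.05) agrees:

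| Slopes in the four conditions | Pooled slope significant | 3-df test rejects |
|---|---|---|
| 0.3, 0.3, 0, 0 | 85% | 71% |
| 0.3, 0.3, 0.3, −0.3 | 85% | >99% |
| 0.3, 0, 0, 0 | 31% | 57–58% |
| 0.5, 0, 0, 0 | 70% | 97–98% |
| 0.3, 0.3, −0.3, −0.3 | 6% | >99% |
| 0.3 in all four | 100% | 4–5% |

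**5. Would a simple decision rule be enough?** Suppose a marker counts as transdiagnostic when the pooled slope is significant, all four estimates share its sign and the 3-df test does not reject. Simulated rates of the label are about 94% for a true common slope of 0.3, 16–17% for (0.3, 0.3, 0, 0), 7% for (0.3, 0, 0, 0), and 35% for (0.3, 0.3, 0.3, 0). The rule helps greatly against the pooled slope alone, but still passes a marker absent in one condition about one time in three.

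**The case against.** The best defence is that the article never says a significant pooled coefficient makes a marker transdiagnostic. The Discussion's wording is exploratory, the study disclaims causal conclusions, and sizing each group at 100 for 10 covariates, with similar results expected by condition, hints at models within each condition. The decision criterion is indeed inferred. But the Statistical Analysis section describes no within-condition main model and no other criterion, so the pooled coefficient is the natural reading. Nor does it help that the study does not aim to compare groups, since showing that something is shared requires looking at each group. The handling of etiology is also something the article itself states, not a detail left to a fuller document.

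Three stronger readings are tempting and are not supported.

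- A reader might infer that any marker active in a single condition would be declared transdiagnostic. At the article's own 0.3 the pooled slope is significant in only about 31% of trials; about 70% needs a slope of 0.5. If two conditions have opposite slopes to the other two, they cancel (6%).
- A reader might infer that the disease-specific covariates, each defined in one condition ("the stroke side, the level of spinal cord injury, the degree of bone deformity of knee OA, and the level of lower limb amputation"), leave no complete case. That requires coding them as missing elsewhere and deleting incomplete cases, and the article states neither. Coding them as zero outside their own condition keeps 400 of 400 patients with a full-rank design.
- A reader might infer that a dummy per etiology plus an intercept is rank-deficient. The article does not say that all four are fitted alongside an intercept, and dropping a reference level is routine. Both of these are ordinary coding detail for an analysis plan.

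**Conclusion.** The concern holds for the common slope. The stated model assumes equal slopes and therefore cannot support the conclusion that a marker-improvement relation is shared across etiologies. The clearest exposure is a marker active in two of the four conditions, or one reversed in a single condition: about 85% of trials would show a significant pooled slope. For a marker active in one condition the risk is smaller but well above the nominal 5%. These figures rest on an assumed two-sided 0.05 level, 100 analysed patients per condition, equal marker variance and no dropout; unequal groups or variances would change the weights in the average but not the logic. The point concerns interpretation of the pooled coefficient and does not make the pooled model itself invalid.

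**What to change.** Keep the pooled model and, before analysis:

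1. Add marker-by-etiology terms (3 df per marker) and report the heterogeneity test.
2. Report the marker slope with its 95% confidence interval in each of the four conditions.
3. Base any transdiagnostic statement on those four estimates (same direction, intervals shown) together with the heterogeneity test. State explicitly that a non-significant interaction alone is not evidence of commonality, since its power is only about 58 to 71% when the slope is 0.3 in one to three conditions and zero in the rest.

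Requiring separate significance in all four conditions would be too strict as the criterion: under a true common slope of 0.3 it is met in only about 55% of trials.

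The cost is wording in the analysis plan, three degrees of freedom per marker out of 400 patients, and fewer markers qualifying. Data collection is unchanged.

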### Inclusion Criteria

Participants of both sexes will be included in the study if they are older than 18 years, have confirmed clinical stability verified by medical evaluation, have signed the informed consent form, and if they fulfill the eligibility criteria for the IMREA rehabilitation program. To be included in the specific injury groups, patients will have to have a clinical, and radiological [magnetic resonance imaging (MRI) or computerized tomography; or bilateral knee radiography] diagnosis of stroke (confirmed by computed tomography scan and/or MRI), spinal cord injury, or knee OA (clinically confirmed) or a clinical diagnosis of bilateral or unilateral lower limb amputation.

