### Exclusion Criteria

Subjects will be excluded if they are pregnant, have active OA with clinical manifestations in joints other than the knee, or if they have any other clinical or social conditions that interfere with the patient's participation in the rehabilitation treatment.

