### Clinical and Functional Assessments

At the beginning of the study, on the participant's first visit, a trained physician will take the patient's history, perform a physical examination, and review the eligibility criteria for that patient. The obtained information from the patient's history such as age, sex, height, weight, ethnicity, education level, medications in current use, comorbidities, and the specific characteristics of each injury will be used as covariates in the final linear regression model.

Several instruments that allow the global assessment of participants, general or specific to each condition, were selected (Table 1 and Appendix 1). Some scales, such as cognitive, sleep, and mood scales, will be used to characterize the study's sample, as well as for the management of confounding variables on the multivariate statistical model.

**Table 1 T1:** Assessment instruments used for each study group.

**Category**	**Instrument**	**Amp**.	**Stroke**	**OA**	**SCI**	**CG^*^**
Independence	Functional Independence Measure (FIM) (11)	X	X	X	X	X
Independence (Specific to SCI)	Spinal Cord Injury Independence Measure (SCIM III) (12)				X	
Cognition	Montreal Cognitive Assessment (MOCA) (13)	X	X	X	X	X
Cognition (speach)	Semantic verbal fluency test (14)		X			
Pain	Conditioned Pain Modulation (CPM) (15)	X	X	X	X	X
Pain	Pressure Pain Threshold (PPT) (16)	X	X	X	X	X
Pain/Sensitivity	Monofilament Sensitivity Test (17)	X	X	X	X	X
Pain/Sensitivity	Tuning Fork Vibration Sensitivity Test (18)	X	X	X	X	X
Pain	Pain Catastrophizing Scale (19, 20)	X	X	X	X	
Pain	McGill Pain Questionnaire (Brazilian Version) (21)	X	X	X	X	
Pain	Visual Analogue Scale (VAS) for Pain (22)	X	X	X	X	
Lower Limb Motor Function	6-min and 10 meters gait test (23)	X	X	X	X	X
Lower Limb Motor Function	Timed Up and Go (TUG) (24)	X	X	X	X	X
Lower Limb Motor Function	Lower Limb Isokinetic Dynamometer (25)	X	X	X	X	X
Lower Limb Motor Function	Walk Index for Spinal Cord Injury (WISCI-II) (26)				X	
Upper Limb Motor Function	Fugl–Meyer Assessment (FMA) (27)		X		X	
Upper Limb Motor Function	Hand Grip and Pinching (28–30)		X		X	X
Upper Limb Motor Function	Purdue Pegboard Test (PPBT) (31)		X		X	X
Upper Limb Motor Function	Robot-Measured Kinematic Variables (32)		X		X	X
Upper Limb Motor Function	Finger Tapping (FT) (33)		X		X	X
Upper and Lower Limb Motor Function	Medical Research Council Scale (MRC) (34)		X	X	X	
Balance	Force platform (35)	X	X	X	X	X
Balance	Berg Balance Scale (36)	X	X	X	X	

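### The upper-limb Fugl–Meyer analysis set is defined by diagnosis alone, so patients with no arm deficit enter it and pull the pooled biomarker–recovery slope toward zero

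*Protocol article*

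**What the plan says.** The Statistical Analysis section of the protocol article describes a regression with motor improvement as the outcome and change in inhibitory markers as predictors, plus a dummy variable for each etiology. It then adds an upper-limb version: "the motor function of the upper limb will only be assessed for patients with stroke and spinal cord injury", with the Fugl–Meyer as the main scale, and "an analysis similar to the one described earlier will be performed but only including these two populations".

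No other section narrows that set:

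- **Inclusion Criteria.** SCI is admitted on diagnosis: "diagnosis of stroke (confirmed by computed tomography scan and/or MRI), spinal cord injury, or knee OA (clinically confirmed". No lesion level or arm impairment is required.
- **Exclusion Criteria.** None concerns lesion level or arm function.
- **Table 1.** The Fugl–Meyer is marked for the whole stroke and SCI columns, with no footnote limiting it.
- **Statistical Analysis, covariates.** Disease-specific features to be tested include "the level of spinal cord injury, the degree of bone deformity of knee OA, and the level of lower limb amputation". No interaction between lesion level and marker is mentioned.

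**The concern.** Amputee and knee osteoarthritis patients are left out of this analysis, evidently because the arm is not their impaired limb. An SCI patient with a lesion below the segments that supply the arms is in the same position but stays in, because the filter is diagnosis and not deficit. So does a stroke patient whose arm is unaffected. Such patients score at or near the maximum before and after rehabilitation, so their change is about zero whatever the marker does.

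This analysis matters because TMS is recorded from a hand muscle and fNIRS uses hand tasks, so it is where marker and scored limb match most directly. The coefficient would be read as the strength of the link between change in inhibition and arm recovery. With patients who cannot recover on the scale mixed in, it understates that link.

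**Working it through.** **Inputs from the article.** 100 stroke and 100 SCI patients, so 200 in this analysis. The Sample Size section gives an effect size of about 0.3 with 10 covariates and n = 100 per group.

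**The plan's own figure.** The article states neither alpha, power nor the effect metric, so the 0.3 cannot be formally reproduced. Assuming two-sided alpha 0.05 and reading it as a partial correlation, n = 100 with 10 predictors gives power 0.875. That reading is plausible, and 0.30 is used below as the true standardised slope β in patients with an arm deficit.

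**Assumptions (not in the article).**
- A share p of the 100 SCI patients has no arm deficit: 30%, 50% or 70%.
- Their Fugl–Meyer change is zero, inferred from the scale ceiling. In practice it would be near zero with measurement noise.
- All stroke patients have a deficit. Any who do not add to the effect.
- The marker SD is 1 in impaired patients and s in unimpaired patients.

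**Slope.** With mean marker change equal across groups, the pooled least-squares slope weights each group by its marker sum of squares:

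pooled slope = β × (200 − 100p) / (200 − 100p + s² × 100p)

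| p | s = 1 | s = 0.5 |
|---|---|---|
| 30% | 0.30 × 170/200 = 0.255 | 0.30 × 170/177.5 = 0.287 |
| 50% | 0.30 × 150/200 = 0.225 | 0.30 × 150/162.5 = 0.277 |
| 70% | 0.30 × 130/200 = 0.195 | 0.30 × 130/147.5 = 0.264 |

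With s = 1 this is β(1 − p/2), a loss of 15% to 35%. With s = 0.5 the loss is 4% to 12%.

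**Does the lesion-level covariate help?** As a main effect it absorbs the difference in mean change but leaves one common slope. Simulation with s = 1 (3,000 runs) gives slopes of 0.257, 0.224 and 0.195 with the covariate in the model, against 0.257, 0.226 and 0.193 without it. Restricting to impaired patients returns 0.300, 0.300 and 0.298.

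**Power in the same simulation** (s = 1, mean change 1 SD in impaired patients):

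| True slope | p | Etiology dummy only | Plus level main effect | Restricted |
|---|---|---|---|---|
| 0.30 | 30% | 0.963 | 0.978 | 0.982 |
| 0.30 | 50% | 0.931 | 0.963 | 0.956 |
| 0.30 | 70% | 0.892 | 0.931 | 0.935 |
| 0.20 | 30% | 0.686 | 0.722 | 0.750 |
| 0.20 | 50% | 0.626 | 0.691 | 0.688 |
| 0.20 | 70% | 0.562 | 0.633 | 0.617 |

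Once level is in the model, restriction brings no consistent gain in power. What it changes is the estimate.

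**The case against.** **The wording may only name the etiologies.** The sentence separates stroke and SCI from the other two groups, and the exact set could be settled in a fuller document. The rehabilitation programme's own eligibility rules are not shown, and lesion level would vary even in a purely cervical group, so the presence of lower lesions is an inference. This stands as a limit on how large the effect is. It does not remove the point: the article states an analysis set, by diagnosis, and nothing in it limits SCI to lesions affecting the arms.

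**Marker change may vary less in patients with intact arms.** This stands. The article gives no information either way, and half the SD makes the bias small.

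**Power.** A reader might infer that the plan loses much power and that restriction regains it. The article does not support that, because it names lesion level among the covariates to be tested, and with that covariate power is about the same as after restriction. With half the marker SD the all-patient model can even show higher nominal power (0.966 against 0.936 at p = 70%).

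**Stroke-specific markers.** A reader might also infer that a marker shared by both conditions would be declared specific to stroke. That needs a comparison between etiologies. The Sample Size section says comparing injury groups is not the aim, and the model has etiology dummies without etiology-by-marker interactions.

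**The all-patient slope is a legitimate estimand.** It is an average that includes patients who cannot improve, and it depends on the case mix recruited. It can be reported, but it does not measure how closely the marker tracks arm recovery. Table 1 lists other upper-limb tests, but the Fugl–Meyer is named as the main scale and the same populations apply.

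**Conclusion.** The point holds in a limited form. Following the plan as written puts patients without an arm deficit into the Fugl–Meyer regression, and the pooled slope is biased toward zero. The lesion-level main effect does not correct this. For a true slope of 0.30 and 30% to 70% of SCI patients unimpaired, the expected estimate runs from 0.255 down to 0.195 with equal marker variance, and from 0.287 down to 0.264 with half the marker SD in unimpaired patients. Both the share and the SD ratio are assumptions, as is a change of zero at the ceiling. The direction is firm; the size is uncertain and could be small. It concerns an additional analysis, not the primary one, and the argument rests on the slope and not on power. It should be corrected, but it does not threaten the study's main result.

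**What to change.** In the Statistical Analysis section, define the main set for the upper-limb analysis as stroke and SCI patients with an upper-limb deficit at baseline. Take this as a Fugl–Meyer upper-limb score below a prespecified near-ceiling cut-off and, for SCI, also a lesion level that affects the arms. A near-ceiling cut-off is better than merely below maximum, which would still admit patients with almost no room to improve. Keep the all-patient model as a sensitivity analysis, preferably with a deficit-by-biomarker interaction so that impaired patients have their own slope.

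The cost is a sentence or two and no new data: the Fugl–Meyer and lesion level are already collected. The downside is a smaller n, for example 150 instead of 200 if half the SCI patients are unimpaired (200 − 50). The cut-off should be fixed before results are seen.

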Spasticity	Modified Ashworth (37)		X		X	
Sleep	Epworth sleepiness scale (38)	X	X	X	X	X
Mood	Hamilton Depression Rating Scale (HAM-D) (39)	X	X	X	X	X
Mood	Hospital Anxiety and Depression Scale (HADS) (40)	X	X	X	X	X
Pain, rigidity, and daily activities	Western Ontario and McMaster Universities Osteoarthritis Index (WOMAC) (41)			X		
Lower limb	Amputee Mobility Predictor (AMP) (42)	X				
Amputation	Quebec User Evaluation of Satisfaction with Assistive Technology (QUEST 2.0) (43)	X				
Stroke	National Institutes of Health Stroke Scale (NIHSS) (44)		X			
SCI	American Spinal Injury Association Impairment Scale (ASIA) (45)				X	
OA	Kellgren-Lawrence Radiographic Classification of OA (46)			X		
OA	Ultrasound Assessment (US)			X		
Quality of life	Stroke Impact Scale (SIS) (47)		X			
Quality of life	Medical Outcomes Short-Form Health Survey (SF-36) (48)	X	X	X	X	X
Polymorphisms	Genetic Polymorphism Analysis (49)	X	X	X	X	X

* *Control group*.

The same evaluator will preferably carry out assessments. Evaluators will be trained to standardize questionnaire applications to reduce assessment subjectivity.

A detailed explanation of all the scales and tests used in this study under Supplementary Material.

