In the statistical analysis for the results of the obtained polymorphisms, classical methods of case–control studies' epidemiological analysis will be applied. Odds ratio and the respective 95% confidence intervals will be estimated by unconditional logistic regression to simultaneously control potential confounding variables. To assess the relationship between the dependent variable (stroke and its subtypes) and the independent variables (polymorphisms of the evaluated genes, smoking, lipid variables, etc.), the statistical technique used will be logistic regression analysis, which allows the evaluation of disease risk associated with a given variable considering all other independent variables in the model.

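### Polymorphisms are planned in all five groups, but the only genetic analysis described targets stroke risk in prevalent rehabilitation patients and is not tied to the study's question about inhibition and recovery

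*Protocol article*

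**What the plan says.** - **Who is genotyped.** In Table 1 (Clinical and Functional Assessments), the row "Genetic Polymorphism Analysis (49") is marked for amputation, stroke, osteoarthritis, spinal cord injury and the control group.
- **Numbers.** Under Participants and Study Design, "400 patients will be recruited, 100 patients with a stroke diagnosis, 100 with knee OA, 100 with spinal cord injury, and 100 amputee patients". Also, "The control group will be made up of 100 healthy subjects paired by sex and age".
- **Genetic analysis.** The last paragraph of Statistical Analysis says that "classical methods of case–control studies' epidemiological analysis will be applied". It continues: "Odds ratio and the respective 95% confidence intervals will be estimated by unconditional logistic regression to simultaneously control potential confounding variables". The relationship to be assessed is between "the dependent variable (stroke and its subtypes) and the independent variables (polymorphisms of the evaluated genes, smoking, lipid variables, etc"), by logistic regression, "which allows the evaluation of disease risk associated with a given variable considering all other independent variables in the model".
- **Aim.** The Introduction sets out to relate biomarkers to functional impairment whatever the cause. Sample Size says that the injury groups are not to be compared; the interest is in what they share. The Discussion repeats that the question is not tied to one etiology.
- **Main model.** Statistical Analysis takes motor improvement as the outcome and changes in inhibitory activity as the predictors. It lists demographic, clinical and disease-specific covariates. Genotype is not among them.

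**The concern.** The genetic data are planned for the whole cohort, but the analysis written for them answers a different question. An analyst who follows the text would estimate the association of each variant with having had a stroke. That says nothing about who recovers, or about the level of inhibition, which are the subjects of the study.

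The stroke analysis also has a difficulty of its own. Its cases have survived, been diagnosed, become clinically stable and been admitted to rehabilitation. A variant that affects survival, residual disability or referral can then show an odds ratio away from 1 without affecting the risk of stroke. Calling the result disease risk invites that misreading. At stake are the usefulness of the genotyping and the interpretation of one ancillary result.

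**Working it through.** **1. Genotyping against stated outcomes.** The plan gives no sample size, power or effect size for the genetic analysis, so there is no figure to reproduce. The check is mainly a comparison of sections.

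| Item | What the article states |
|---|---|
| Groups genotyped | All five (Table 1) |
| Outcome named for genotype | Stroke and its subtypes only |
| Stated purpose | Disease risk |
| Genotype in the main model's covariate list | No |
| Genotype in the Discussion's list of candidate biomarkers | No; the list covers EEG, TMS, fNIRS and MRI measures |
| Stated analysis of genotype against inhibition or recovery | None |

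**2. Source of the cases.** Patients enter on admission to the rehabilitation programme (Participants and Study Design). They must be clinically stable (Inclusion Criteria) and have no condition that interferes with participation (Exclusion Criteria). The stroke cases are therefore prevalent and selected. An odds ratio from such cases combines any effect on incidence with any effect on survival and on selection into rehabilitation. The size and direction of the second part cannot be worked out, because the article does not name the genes.

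**3. Comparators.** The paragraph does not say who is compared with the stroke cases.
- Patients without stroke: 400 − 100 = 300.
- All participants without stroke: 300 + 100 healthy controls = 400.
- The comparators could therefore be 100 healthy controls, 300 other patients, or all 400.

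**4. Illustration of scale (assumptions, not figures from the plan).** Assume two-sided alpha 0.05, power 80%, and carrier frequency p0 among comparators between 0.2 and 0.5. For an odds ratio OR, the carrier frequency in cases is

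p1 = p0·OR / (1 − p0 + p0·OR).

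With n1 cases, n0 comparators and pooled frequency p̄,

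power = Φ[(|p1 − p0| − 1.96·√(p̄(1 − p̄)(1/n1 + 1/n0))) / √(p1(1 − p1)/n1 + p0(1 − p0)/n0)].

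Example with p0 = 0.3 and 100 against 100:
- OR = 2.27 gives p1 = 0.493 and p̄ = 0.396.
- The null standard error is 0.0692 and the alternative one 0.0678.
- (0.1927 − 1.96 × 0.0692) / 0.0678 ≈ 0.84, which is 80% power.

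Solving for the smallest detectable OR with 100 cases:

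| p0 | 100 comparators | 300 comparators | 400 comparators |
|---|---|---|---|
| 0.2 | 2.44 | 2.06 | 2.01 |
| 0.3 | 2.27 | 1.94 | 1.90 |
| 0.4 | 2.22 | 1.91 | 1.87 |
| 0.5 | 2.26 | 1.94 | 1.89 |

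The range is 2.22 to 2.44 with 100 comparators and 1.87 to 2.06 with 300 or 400. Stroke subtypes would have fewer cases and so larger detectable odds ratios. No allowance is made for testing several genes. These figures show what the stroke analysis could detect. They do not measure bias or relevance to the study's aim.

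**The case against.** Several points on the other side have force.

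- **Unused data.** A reader might infer that the genotypes of the 300 patients without stroke go unused. The article does not support this. If the comparators are everyone without stroke, all 300 enter the model. The opening sentences on case-control methods and odds ratios also apply to the polymorphisms in general; stroke is named only afterwards. What stands is that the comparators and the role of the other three conditions are not stated.
- **Estimability.** A reader might infer that the design cannot estimate disease risk at all, or that the cases are hospital inpatients. Neither follows. A case-control analysis can estimate odds ratios, which is what the plan promises, and the article speaks only of admission to a rehabilitation programme. Bias from prevalent cases is possible, not demonstrated.
- **Matching and lipids.** The article says that controls are paired by sex and age, but not how. It names lipid variables without describing their measurement. It is condensed and refers to an appendix and supplementary material that are not shown, so neither silence counts as an error.
- **Confounders.** Adjustment for potential confounders is already planned, and age, sex and ethnicity are collected. Asking for these three by name is a modest tightening.
- **Importance.** The genetic analysis does not enter the main model, the sample-size reasoning or the biomarker classification.

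These points narrow the concern and lower its weight. They do not remove the mismatch: the article positively specifies an outcome and a purpose that lie outside its own aims.

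**Conclusion.** The concern holds in limited form, and its severity is minor. Genotyping covers five groups, the only named genetic outcome is stroke and its subtypes, and nothing stated connects genotype to inhibition or motor recovery. The odds ratios would come from prevalent, clinically stable patients in rehabilitation against unspecified comparators, so disease risk is too strong a label for them.

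This conclusion rests on the text alone and needs no numerical assumption. The detectable odds ratios depend on assumed carrier frequencies, alpha and power, and serve only as background. No primary conclusion of the study changes.

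**What to change.** In the genetic paragraph of Statistical Analysis:

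1. Make the genetic analysis a regression of motor improvement, adjusted for baseline, on genotype across all genotyped patients. Add a second regression with baseline inhibition as the outcome. Adjust both for etiology, age, sex and ethnicity, and label them exploratory.
2. If the stroke odds ratio is kept, name the comparators and include age, sex and ethnicity in the model. Replace disease risk with association in prevalent rehabilitation cases. Keep lipid terms only if lipids are measured.

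The cost is a change of wording. The genotypes, the clinical and neurophysiological measures and the covariates are already planned. What is given up is the strength of the stroke-risk claim, which becomes descriptive.
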